**Studies investigating the effect of diet + PA during pregnancy**

| Study reference                                                    | Type of study | Target population                                                    | Intervention                                                                                                                                  | Findings                                                                                                                                          |
|--------------------------------------------------------------------|---------------|----------------------------------------------------------------------|-----------------------------------------------------------------------------------------------------------------------------------------------|---------------------------------------------------------------------------------------------------------------------------------------------------|
| Vinter et al. 2011 (Ref 41)
Lifestyle in Pregnancy (LiP) study. | RCT           | 360 obese (pre-pregnant BMI 30-45 kg/m  ) pregnant women | Intervention program included dietary guidance + moderate PA for 30-60 min daily + closed training sessions with instructor for 1 h each week | Intervention group had a significantly lower median (range) GWG compared with the control group of 7.0 (4.7–10.6) vs. 8.6 kg (5.7–11.5; P = 0.01) |

Date and version No: 18th July 2019, Version 4.2

|                                                                                                                    |     |                                                                                                                           |                                                                                                                                                                  |                                                                                                                                                                                                                            |
|--------------------------------------------------------------------------------------------------------------------|-----|---------------------------------------------------------------------------------------------------------------------------|------------------------------------------------------------------------------------------------------------------------------------------------------------------|----------------------------------------------------------------------------------------------------------------------------------------------------------------------------------------------------------------------------|
| Renault et al. 2014 (Ref 42)
Treatment of Obese Pregnant Women (TOP) study.                                     | RCT | 425 obese pregnant women comparing 3 groups                                                                               | PA + Diet, (n = 142)
PA intervention (daily step count of 11,000 steps/day every day for 4 weeks (n = 142)
Control group receiving standard care (n = 141) | PA intervention decreased GWG by a mean of 1.38 kg (P = 0.040).                                                                                                                                                            |
| Koivusalo et al 2016. (Ref 43)
The Finnish Gestational Diabetes Prevention Study (RADIEL study).                | RCT | 293 pregnant women with a history of GDM and/or a pre-pregnancy BMI of $\geq 30$ kg/m  at <20 weeks gestation | Intervention group received individualized counselling on diet, physical activity, and weight control. control group received standard antenatal care            | GDM incidence was 13.9% in the intervention group and 21.6% in the control group ([95% CI 0.4-0.98%]; P = 0.044).
GWG was significantly lower in the intervention group (p=0.037)                                       |
| Dodd et al. 2014 (Ref 44, 45)
Limiting weight gain in overweight and obese women during pregnancy (LIMIT) trial | RCT | 2,152 singleton pregnant mothers between 10-20 weeks GA and BMI $\geq 25$ kg/m                                | Diet and lifestyle advice group (n=1,075) vs standard care (n=1067)                                                                                              | Risk of LGA babies were similar in both groups
Babies of life-style advice group had higher mid-thigh fat mass measured by US and rate of adipose tissue deposition was slow in this group compared with control group. |

Date and version No: 18th July 2019, Version 4.2

|                               |                                     |                                                                                                                                                                      |                                                                                                             |                                                                                                                                                                                                                      |
|-------------------------------|-------------------------------------|----------------------------------------------------------------------------------------------------------------------------------------------------------------------|-------------------------------------------------------------------------------------------------------------|----------------------------------------------------------------------------------------------------------------------------------------------------------------------------------------------------------------------|
| Bennet et al. 2018 (Ref 46)   | Systematic review and meta-analysis | 45 RCTs                                                                                                                                                              | -                                                                                                           | Diet and PA interventions aimed to reduce GWG was associated with reduced GDM risk by 44% and 38% respectively. Among Asian the risk reduction with diet and life-style 62% and 32% respectively                     |
| Shepherd et al. 2017 (Ref 47) | Cochrane Database Systematic Review | 23 RCTs and cluster-RCTs, comparing combined diet and exercise interventions with no intervention (i.e. standard care), that reported on GDM diagnosis as an outcome | -                                                                                                           | Reduced GDM risk in intervention group compared with the standard care group (average risk ratio (RR) 0.8, 95% CI 0.71 to 1.01. Reduced risk of caesarean section (RR 0.95, 95% CI 0.88 to 1.02) in intervention arm |
| Petrella et al. 2014 (Ref 48) | Case-control study                  | Singleton pregnant women with BMI >25 kg/m                                                                                                               | Therapeutic lifestyle changes (diet 1800kcal/day + mild PA 30min/d thrice weekly) (n=33) vs Controls (n=28) | Lower GWG, lower incidence of GDM, hypertensive disorders and preterm births in the intervention group compared to controls.                                                                                         |

Date and version No: 18th July 2019, Version 4.2**4. OUTCOME MEASURES**

| Outcomes                                                       | Measurements                                                                                                                                               | Timepoint(s) of evaluation of this outcome measure (if applicable)                                      |
|----------------------------------------------------------------|------------------------------------------------------------------------------------------------------------------------------------------------------------|---------------------------------------------------------------------------------------------------------|
| Primary objective                                       |                                                                                                                                                            |                                                                                                         |
| Incidence of GDM                                               | Fasting plasma glucose
Glucose at 1 hour and 2 hours' post 75g OGTT (according to IADPSG criteria) or Fasting hyperglycemia measured by fasting glucose | Between weeks 26-28

At 32 weeks                                                                  |
| Secondary objective                                     |                                                                                                                                                            |                                                                                                         |
| Effect of intervention on fasting blood glucose concentration  | Fasting plasma glucose                                                                                                                                     | Between weeks 26-28 and at 32 weeks of gestation                                                        |
| Trial and post-trial surveillance measures              |                                                                                                                                                            |                                                                                                         |
| Gestational weight gain                                        | Maternal weight                                                                                                                                            | At screening, run-in-phase, randomization, visits 1,2,3 and at delivery (before the birth of the child) |
| Gestational hypertension                                       | Maternal blood pressure                                                                                                                                    | At screening, run-in-phase, randomization, visits 1,2,3 and at delivery (before the birth of the child) |
| Proportion of women undergoing Instrumental/caesarean delivery | Instrumental/caesarean delivery (elective and emergency)                                                                                                   | At delivery                                                                                             |
| Post-partum haemorrhage (primary)                              | Amount of blood loss within 24 hours of child birth                                                                                                        | From delivery to 24 hours                                                                               |
| Blood loss at delivery                                         | Amount of blood lost during delivery                                                                                                                       | At delivery                                                                                             |
| Pre-eclampsia and eclampsia                                    | Clinical diagnosis (hypertension + proteinuria +/- seizures)                                                                                               | Clinical diagnosis after 28 weeks of GA                                                                 |
| Pre-term births (<37 weeks of gestational age)                 | Gestational age calculated from dating scan                                                                                                                | At birth of the new born                                                                                |
| Foetal macrosomia                                              | Birth weight (defined as birth weight >2 SDs above the population-specific mean in each setting)                                                           | At birth of the new born                                                                                |
| Birth weight                                                   | Birth weight                                                                                                                                               | At birth of the new born                                                                                |
| APGAR score at 1 and 5 min of birth                            | Clinically recorded APGAR score                                                                                                                            | At birth of the new born                                                                                |

Date and version No: 18th July 2019, Version 4.2

|                                              |                                       |                             |
|----------------------------------------------|---------------------------------------|-----------------------------|
| Length of the new born                       | Length measured from head to the heel | Within 48 hours of birth    |
| Barriers to interventions in pregnancy 1 & 2 | Questionnaire based assessment        | At screening
At 32 weeks |

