|  | 
intervention (yoghurt and PA) on adverse maternal and new-born outcomes.
               | 
delivery (elective and emergency) captured on delivery records by treating obstetrician
 
 
• Post-partum haemorrhage (Primary) as captured on delivery records by treating obstetrician
 
• Pre-eclampsia and eclampsia based on blood pressure recording at each visit
 
• Blood loss at delivery as captured on delivery records by treating obstetrician
 
 
New born outcomes
 
 
• Pre-term births (<37 weeks of gestational age) calculated from the ultrasound derived gestational age captured at screening visit dating scan.
 
• Foetal macrosomia (defined as birth weight >2 SDs above the population-specific mean in each setting)
 
• Birth weight and length
 
• APGAR score at 1 and 5min of after birth
 
 |
|  | 
(iii) To determine social and cultural barriers to life-style changes during pregnancy
 | 
Questionnaire based assessment of social and cultural barriers.
                                                                                                                                                                                                                                                                                                                                                                                                                                                                                                                                                                                                                                                                                                                                                                                                                  |

Date and version No: 18th July 2019, Version 4.2**2. ABBREVIATIONS**

|        |                                                                      |
|--------|----------------------------------------------------------------------|
| AC     | Abdominal circumference                                              |
| ACOG   | American College of Obstetrics and Gynaecology                       |
| AE     | Adverse event                                                        |
| AFVI   | Amniotic Fluid Volume Index                                          |

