### Hypothesis

Daily yoghurt and/or daily walking for at least 14 weeks will reduce the risk of developing gestational diabetes in 'high-risk' pregnant women

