## 5. STUDY DESIGN

**Design:** 2 x 2 factorial design, multi-centric, open labelled, randomized controlled trial

**Total study duration:** 36 months

**Number of scheduled visits:** 5

- (i) **Screening visit (visit -2,  $\leq 16$  weeks GA):** Singleton pregnant women willing to participate in the study will be assessed for eligibility based on inclusion/exclusion criteria and eligible participants will be asked to sign an informed consent if willing to participate. Eligible women will undergo an oral glucose tolerance test (OGTT) to rule out impaired glucose intolerance or diabetes at screening and will also undergo dating ultrasound scan. Routine antenatal examination will be done. Barriers to life-style interventions-1 during pregnancy will be assessed using a questionnaire.
- (ii) **Run-in visit (visit -1,  $\leq 17$  weeks GA):** Baseline assessments of dairy product consumption will be done using standardized questionnaire. Additionally, objective measurements of baseline PA activity over 7 days will be assessed in all study participants (with the result blinded to participants) using a wearable accelerometer device (Garmin Vivofit 4 fitness band).
- (iii) **Randomization ( $\leq 18$  weeks GA):** Women will be randomized to either (i) diet (consumption of 200g of yoghurt per day), (ii) PA (a minimum of 40% increase above the recorded baseline PA) (iii) diet and PA or (iv) standard care. Active intervention will be from randomization to 32 weeks of GA.
- (iv) **Visit 1 (18-20 weeks GA):** maternal weight, blood pressure, routine antenatal examination and foetal morphology scan.
- (v) **Visit 2 (26-28 weeks GA):** maternal weight, blood pressure, routine antenatal examination and OGTT. Primary endpoint (diagnosis of GDM based on IADPSG criteria) will be assessed at this visit. Women with GDM will continue on allocated study intervention until end of study (week 32) in addition to the clinical management provided as per the local obstetric practice.
- (vi) **Visit 3 (32 weeks GA, End of Study visit):** maternal weight, blood pressure, routine antenatal examination, ultrasound foetal scan and fasting blood glucose and barriers to pregnancy intervention-2 assessment. (A repeat ultrasound scan at this stage is based on the evidence that growth restriction although starts in early pregnancy, is more marked between 22-34 weeks and also that foetal measurements do not have

Date and version No: 18th July 2019, Version 4.2

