#### 7.5.3. Baseline assessment at Randomization (Visit: 0; week ≤18)

- I. **Weight:** Weight of the mother will be recorded as described in 7.5.1 (II)
- II. **Blood pressure:** Systolic and diastolic BP of the mother will be recorded as described in 7.5.1 (III)

Date and version No: 18th July 2019, Version 4.2

- III. **Antenatal examination (fundal height):** Routine antenatal examination including fundal height will be recorded as described in 7.5.1 (IV)
- IV. **Intervention allocation**
- V. **Compliance assessment:** to interventions (step count, yoghurt diary)
- VI. **Safety assessments** to interventions (e.g. adverse events and/or SAE assessment)
- VII. **Concomitant medication** assessment.

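### The synopsis and section 4 define the pre-eclampsia/eclampsia outcome differently, and section 4 read literally leaves diagnoses before 28 weeks out of that outcome

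*Protocol*

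**What the plan says.** The outcome appears twice in the current text of the protocol (version 4.2).

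- **Section 1, Synopsis, trial and post-trial surveillance, maternal outcomes:** "Pre-eclampsia and eclampsia based on blood pressure recording at each visit". The line mentions neither proteinuria nor a lower limit of gestational age. It sits under an objective on the safety and efficacy of the "intervention (yoghurt and PA) on adverse maternal and new-born outcomes".
- **Section 4, Outcome Measures, row for pre-eclampsia and eclampsia:** the measurement column reads "Clinical diagnosis (hypertension + proteinuria +/- seizures", and the column for the time of evaluation reads "Clinical diagnosis after 28 weeks of GA".

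Four other places bear on the point.

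- Section 4 has a separate row for gestational hypertension, measured by maternal blood pressure. Its timing is "At screening, run-in-phase, randomization, visits 1,2,3 and at delivery (before the birth of the child", with no 28-week floor.
- Section 5 gives the treatment period: "Active intervention will be from randomization to 32 weeks of GA". Sections 5 and 7.5.3 put randomisation at 18 weeks or earlier.
- Section 9.2.1 lists pre-eclampsia/eclampsia as an expected serious adverse event (SAE), without a gestational-age limit. It is captured on the SAE form but exempt from timed reporting to the data monitoring committee.
- Section 10.3.3 summarises adverse events and SAEs by intervention group.

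**The concern.** The two definitions differ in criterion and in time window, so they select different women.

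The synopsis names only blood pressure. Followed literally, it would class raised pressure without proteinuria as pre-eclampsia. Those women already belong to the gestational hypertension outcome, so the two outcomes would overlap. It also offers no way to identify eclampsia, which the same line covers.

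Section 4 has a fuller criterion but a narrower window. Followed literally, a case diagnosed on allocated intervention before 28 weeks does not count towards the outcome. The neighbouring gestational hypertension row has no such floor, and the protocol gives no reason for one here.

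At stake is the count in each arm for an outcome that the protocol ties to both safety and efficacy. Participants and investigators know the allocation (section 7.4), so it should be clear before the data are seen which events qualify.

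**Working it through.** **1. The two definitions side by side**

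| | Synopsis (section 1) | Section 4 |
|---|---|---|
| Criterion | Blood pressure recordings | Clinical diagnosis: hypertension and proteinuria, with or without seizures |
| Window | Each visit | After 28 weeks |

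**2. Three example cases under each literal reading**

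| Case | Synopsis | Section 4 |
|---|---|---|
| Raised pressure at Visit 3 (32 weeks), no proteinuria | Counted | Not counted; belongs to gestational hypertension |
| Hypertension with proteinuria, diagnosed at Visit 2 at 26 weeks | Counted | Not counted |
| Hypertension with proteinuria, diagnosed at 34 weeks between study visits | Counted only if pressure is also raised at delivery | Counted |

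The rules disagree in both directions, so neither is simply a stricter form of the other.

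**3. Length of the section 4 gap within the intervention period**

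Inputs:
- week of randomisation r, at most 18 (sections 5 and 7.5.3)
- end of intervention, week 32 (section 5)
- start of the section 4 window, week 28 (section 4)

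Check against the protocol's own figure: 32 − 18 = 14 weeks. This matches the hypothesis in section 3, "Daily yoghurt and/or daily walking for at least 14 weeks".

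Share of intervention weeks before the window opens = (28 − r) / (32 − r):

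| Randomised at week | Intervention weeks | Weeks before 28 | Share before 28 | Share from 28 to 32 |
|---|---|---|---|---|
| 18 | 14 | 10 | 10/14 = 71% | 4/14 = 29% |
| 17 | 15 | 11 | 11/15 = 73% | 4/15 = 27% |
| 16 | 16 | 12 | 12/16 = 75% | 4/16 = 25% |

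Sensitivity check: suppose onset is counted only from 20 weeks. This is an assumption and is not in the protocol. The share is then (28 − 20) / (32 − 20) = 8/12 = 67%.

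**4. What the share does not measure**

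The denominator stops at week 32, but the section 4 window has no stated end and sections 5 and 7.6.4 carry surveillance to delivery. The protocol also gives no incidence or timing for pre-eclampsia. The 71% is therefore a share of intervention weeks and cannot be turned into a share of cases.

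**5. Where early cases go**

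A case diagnosed at 26 weeks is an expected SAE under section 9.2.1 and goes on the SAE form. Section 9.3 has the investigator report all SAEs to the sponsor within 24 hours. Section 10.3.3 then puts the case in the summary by group. It is missing from the pre-eclampsia outcome, but not from the trial's safety data.

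**The case against.** The case on the other side is that this is a mismatch of wording with little consequence.

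- The synopsis does not say that blood pressure is the sole criterion. Because the line also covers eclampsia, it may be shorthand for a data source, with section 4 giving the full criterion.
- The 28-week text is in a column for the time of evaluation. No sentence says that earlier diagnoses are discarded, so it may be descriptive.
- The outcome is neither primary nor, in section 4, secondary. No sample size or significance level rests on it, and an analysis plan commonly settles such derivations.

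Much of this is fair and keeps the point small. It does not remove it. Both cells are live text, nothing says which governs, and an analysis plan would have to depart from one of them.

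A reader might be tempted by four stronger claims that the protocol does not support.

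- *Only Visit 3 and delivery can supply cases under section 4.* A clinical diagnosis is not tied to a study visit. Adverse events are also collected through weekly phone reviews and home visits (section 9.1), so a diagnosis at any time from 28 weeks to delivery could count.
- *Early cases enter no comparison between arms.* They enter the SAE summary by group. The exemption in section 9.2.1 concerns timed reporting to the monitoring committee, not recording.
- *The visit schedule has a gap because it lists no urine protein test.* Antenatal examination follows local obstetric practice (section 7.5.1), and the diagnosis can come from clinical records.
- *Some 71% of cases are missed.* As shown above, the figure counts weeks.

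**Conclusion.** The inconsistency is real and of low severity. The synopsis and section 4 disagree on criterion and window, and each rule, taken at its word, gives a faulty count. The first overlaps gestational hypertension; the second omits diagnoses made between randomisation and 28 weeks. That omitted span is 71% to 75% of the intervention weeks for randomisation at 18 to 16 weeks.

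The conclusion rests on reading both cells literally, and in particular on reading the 28-week entry as a restriction. If it was meant as a description, the omission disappears but the conflict over the criterion and the unclear window remain. The effect is confined to the named outcome. How many cases would change classification cannot be estimated from the protocol.

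**What to change.** Use one outcome definition in sections 1 and 4:

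- **Criterion:** the clinical diagnosis already in section 4, taken from antenatal, SAE or delivery records.
- **Window:** from randomisation to delivery, replacing both the each-visit wording in the synopsis and the 28-week entry in section 4.
- **Blood pressure alone:** raised pressure without the clinical diagnosis is reported under the existing gestational hypertension outcome.

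This changes how an outcome is counted and leaves clinical management as it is. The cost is the wording of two table cells and one case report form field filled from existing records. No extra visit or test is needed, and the sample size is unaffected.
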